### Interim analyses {21b}

Baseline data will be analysed to determine whether key characteristics are evenly distributed between control and intervention arms, and to inform IFPLAN project implementation indicators. We will first assess and report the balance at baseline between the intervention and control arms based on socio-economic factors and any other factors likely to affect the implementation of the intervention.

### Methods for additional analyses (e.g. subgroup analyses) {20b}

Subgroup analysis will be conducted focusing on women identified as having functional difficulty (with or without depression or anxiety). This analysis will be based on the same analytical approach as outlined for the primary and secondary indicators.

For the process evaluation, thematic analysis will be conducted on translated interview transcripts based on project theory, process evaluation domains, and emerging themes on access to family planning. A comparative case study approach will be utilized to compare key themes between women with and without disabilities to better understand the mechanisms of impact for the project and unintended consequences. The comparative case studies and interview data from key health facility staff and intervention implementers will be complemented by programme monitoring data reviewed and synthesized by the study team to further understand the fidelity, dose, adaptions and reach of the interventions implemented.

### Methods in analysis to handle protocol non-adherence and any statistical methods to handle missing data {20c}

We will adopt an intention-to-treat analysis, and therefore health facility catchment areas will be analysed per their original arm assignment even if subsequently the intervention is not implemented in any or all of the health facilities in that cluster. Given that the health facility catchment areas are close together due to the small geographical area of Kaduna city, respondents will be asked about which facility they attend for family planning services and their participation in community-based family-planning activities in order to conduct a sensitivity analysis using an as-treated per-protocol analysis. Furthermore, should health facility staff be transferred between facilities from the intervention arm to control arm (or vice versa) this will be captured through the process evaluation and its potential effects explored.

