### Outcomes {12}

The primary outcome for the trial, as shown in Table 2, is access to modern family-planning methods. We will also measure ‘realized access’, or *use*, as an important secondary outcome, defined as women aged 18–49 with disability who are sexually active and would like to delay or reduce future pregnancies and are using modern family-planning methods to achieve this.

**Table 2 Tab2:** Summary of outcomes for the IFPLAN project’s cluster randomized controlled trial

	**Outcome name**	**Measure**
**Primary outcome**	Access to family planning	Survey: binary (yes / no), based on composite of questions: • Know of at least three modern contraceptive methods that are available; & • Know where to access modern family-planning; & name the location; & list the available family planning services; & • Believe that they could use services if they needed them
**Secondary outcome**	Knowledge of family planning	Survey: binary (yes / no), based on composite of questions: • Know of at least three modern contraceptive methods that are available
	Intention to use	Survey: binary (yes / no), based on: • Will use contraceptive method in the future
	Use of family planning (modern method)	Survey: binary (yes / no), based on composite of questions: • Participant or participant’s partner currently doing something or using any method to delay or avoid getting pregnant; & • (Using a modern contraceptive method)
	Unmet need for family planning	Survey: binary (yes / no), based on composite of questions: • Would prefer to delay or not to have another child & • Not using contraception
	Perceived attitudes towards women with disabilities	• Score based on inclusion and participation module of survey

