### Sample size {14}

Calculations were conducted in Microsoft Excel [31], based on Hayes & Bennett [32]. The assumptions, as summarized in Table 4, were used in determining the likely number of women 18–49 years with disabilities who will be living in the catchment areas of the healthcare facilities, as this is the target population for the evaluation. Various plausible estimates of the between-cluster coefficient of variation (*k*) and effect sizes were explored. Determination of the sample size was guided by the number of areas that the Sightsavers team has capacity and funding to reach, and security concerns limiting implementation to Kaduna city. Assuming *k* = 0.3, a 5% significance level, and 80% power, the trial will be able to detect a risk ratio of 1.5 (i.e. a 50% increase in access compared to the control arm) with 25 women with disabilities interviewed in each cluster. This design will require approximately 20,000 households to be screened for eligible women. It was originally intended to have 19 clusters per arm (a total of 38 clusters overall); however, it was only possible to identify a total of 37 clusters in Kaduna city, consequently 19 clusters were assigned to the intervention arm and 18 clusters to the control arm.

**Table 4 Tab4:** Assumed and derived values for the IFPLAN cluster randomized controlled trial sample size calculations

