**Assumptions:**	
Proportion of women aged 18–49 years	20.0%
Proportion of women 18–49 years who are disabled based on Washington Group Questions^a^	0.7%
Proportion of women 18–49 years with depression or anxiety^b^	6.0%
Estimated overlap between the above	30%
Number of people in each cluster	10,000
Proportion of women who have ‘access’ to family planning	25%

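### The contamination sensitivity analysis merges as-treated with per-protocol and defines exposure by outcome-related behaviour, so it cannot reliably show whether contamination diluted the intention-to-treat result

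*Protocol article*

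**What the plan says.** Section {20c} analyses catchment areas in the arm to which they were allocated, even where the intervention is not delivered. It then notes how close together the catchments are and says that "respondents will be asked about which facility they attend for family planning services and their participation in community-based family-planning activities", and that this is done "in order to conduct a sensitivity analysis using an as-treated per-protocol analysis". The same section says that staff transfers between arms will be captured in the process evaluation and their effects explored.

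The primary outcome in Outcomes {12}, Table 2, is a yes/no composite: knowing three modern methods, "Know where to access modern family-planning; & name the location", listing the services offered, and believing she could use services if needed. Current use of a modern method is a secondary outcome, which the text treats as access realized. Intervention description {11a} presents the community activities as part of the intervention, meant to raise knowledge and confidence and directed at intervention clusters.

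**The concern.** An as-treated analysis regroups people by what they received. A per-protocol analysis removes those who did not receive what was assigned. The label joins the two, so the section does not identify one analysis.

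The larger difficulty is the exposure. Which facility a woman attends for family planning, and whether she joins family-planning activities, are her own choices after randomization. A woman who attends such a facility can almost certainly name it, and she is likelier than others to know methods and to believe she could use services. Women who already have access are therefore likely to be over-represented among attenders and participants in either arm. A comparison that counts only these women as treated mixes self-selection with any intervention effect, and the selection runs towards benefit.

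A contamination check should show whether the intention-to-treat estimate was diluted. If that estimate were null and this analysis gave a large risk ratio, a reader could take it as evidence of dilution when selection alone would explain it.

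**Working it through.** **Design target first.** Sample size {14} assumes k = "0.3, a 5% significance level, and 80% power", with "25 women with disabilities interviewed in each cluster", and concludes that "the trial will be able to detect a risk ratio of 1.5". Table 4 sets the row "Proportion of women who have ‘access’ to family planning" at 25%. The Hayes and Bennett formula for unmatched proportions, with p0 = 0.25, p1 = 0.375, m = 25, k = 0.3 and two-sided 5% (sidedness is not stated), is

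c = 1 + (1.96 + 0.84)² × [p0(1−p0)/m + p1(1−p1)/m + k²(p0² + p1²)] / (p0 − p1)²

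The bracket is 0.0075 + 0.009375 + 0.01828 = 0.03516. Divided by 0.015625 this is 2.25, and c = 18.66 with unrounded normal deviates. That is 19 clusters per arm, and 19 × 25 × 2 = 950 women. The plan's figure reproduces, and 1.5 is the yardstick below.

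**Null truth.** Access is p = 0.25 in both arms. The article gives no attendance or crossover rates, so those below are assumptions, except that 13.7% is the Kaduna modern-method use figure from Background {6a}, used as a proxy for attendance. Half of attenders are assumed to use an intervention-arm facility.

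**Grouping 1: only attenders at an intervention facility count as treated; everyone else is untreated.** Let u1 and u0 be the attendance proportions in women with and without access.

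- Proportion attending: v = p·u1 + (1−p)·u0
- Access among attenders: a = p·u1 / v
- Access among untreated: (p − a·v/2) / (1 − v/2)

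| Assumption | v | a | Untreated | Null risk ratio |
|---|---|---|---|---|
| u1 40%, u0 40% | 0.400 | 0.250 | 0.250 | 1.0 |
| u1 30%, u0 20% | 0.225 | 0.333 | 0.239 | 1.4 |
| u1 40%, u0 10% | 0.175 | 0.571 | 0.219 | 2.6 |
| u1 50%, u0 5% | 0.1625 | 0.769 | 0.204 | 3.8 |
| v = 13.7%, a = 50% | 0.137 | 0.50 | 0.232 | 2.2 |
| v = 13.7%, a = 70% | 0.137 | 0.70 | 0.217 | 3.2 |
| v = 13.7%, a = 90% | 0.137 | 0.90 | 0.202 | 4.5 |

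For the third row: (0.25 − 0.571 × 0.0875) / 0.9125 = 0.219, and 0.571 / 0.219 = 2.6.

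For the secondary outcome of use the overlap is tighter. With 13.7% use, and 60% of users and 5% of non-users attending, 0.0822 / 0.1254 = 66% of attenders are users. Among the untreated the figure is (0.137 − 0.0411) / 0.9373 = 10%. The null ratio is about 6.4.

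**Grouping 2: intervention-arm attenders against control women who do not attend an intervention facility (a per-protocol form).** With a fraction c of attenders crossing, access in the control group is (p − p·u1·c) / (1 − v·c). At 40% versus 10% and c = 20% this is 0.23 / 0.965 = 0.238, a ratio of 2.4. For attendance from 30% versus 20% to 50% versus 5%, and c from 10% to 30%, the null ratio is about 1.34 to 3.4.

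**Grouping 3: only women who cross over are reassigned or dropped; non-attenders stay in their allocated arm.** With equal crossing in both directions, the arms exchange or lose women of the same kind and the null ratio stays at 0.99 to 1.01. Comparing attenders only, by arm of the facility attended, gives the same. A simulation with 37 clusters of 25, k = 0.3 and 20% crossover agreed: median ratios 0.99 to 1.01 here, and 1.4, 2.6 and 3.8 under Grouping 1. Its significance tests ignored clustering, so only the ratios are used.

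If crossing is one-way, with 20% of control attenders moving to intervention facilities, attendance at 40% versus 10% and 100 women per arm, then 3.5 control women cross and 2 of them have access. Reassigning gives (27/103.5) / (23/96.5) = 1.09. Dropping gives 0.25 / 0.238 = 1.05. The bias is small but still favours benefit.

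**The case against.** The strongest reply is that the article gives no rule for women who attend nowhere and join nothing. The stated motive is proximity, so the authors may intend only to move or drop women who cross to an opposite-arm facility, which is nearly unbiased. A grouping rule is commonly left to the analysis plan, and its absence from an article is not an error. This stands, and it makes the bias conditional. What remains is what the article does fix: a label that joins two analyses, and two exposure variables chosen by the woman. On its ordinary meaning, as-treated points to the biased groupings.

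A reader might infer three stronger things that the article does not support:

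- **That attendance and participation are part of the outcome.** Table 2 lists neither. Attendance nearly guarantees naming a location but does not establish knowledge of three methods, and participation is an intervention exposure.
- **That the analysis will show a large benefit under no effect.** It need not. The ratio is 1.0 if attendance is unrelated to access, and close to 1 under Grouping 3.
- **That contamination is otherwise unaddressed.** Facilities within 0.5 km were merged, clusters were separated and overlapping communities removed (Eligibility criteria {10}), and staff transfers are followed in the process evaluation. This is, however, the only quantitative analysis described for women crossing between clusters.

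It is also fair that this is a sensitivity analysis and that nothing in the article gives it inferential weight.

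**Conclusion.** The point holds in conditional form. The section names two analyses as one and bases them on self-selected behaviour after randomization that is closely tied to the primary outcome and to use. Where only attenders or participants count as treated, the null risk ratio is about 1.4 to 4.5 for the primary outcome whenever attendance is commoner among women with access, and most of the settings examined exceed the design target of 1.5. Where only crossovers are reassigned or dropped, the bias is near zero with balanced crossing and small with one-way crossing. A reader could not tell dilution from selection, so the analysis cannot reliably do its job.

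The sizes are illustrations. Attendance by access status, crossover rates and the even split of attenders are assumed; 13.7% is method use among Kaduna women generally, not attendance among women with disabilities; participation was not modelled separately. The intention-to-treat result is unaffected. This is a worthwhile, inexpensive correction and does not threaten the trial's main conclusion.

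**What to change.** Make the contamination check an intention-to-treat analysis by allocated arm, repeated after excluding women who live in communities nearest an opposite-arm cluster. Use the catchment boundaries as refined at the site visits, and set the exclusion rule before endline data are seen. Nearness follows from the map and the draw, not from the woman's behaviour, so the comparison by allocated arm is kept. Report facility attended and activities joined descriptively by arm, as measures of crossover and reach.

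If any as-treated analysis is kept, limit it to reassigning women who attend an opposite-arm facility, leave non-attenders in their allocated arm, and label it exploratory and open to selection bias. Drop the combined label.

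Using allocation as an instrument for reported exposure is a weaker substitute. Town hall meetings, sessions with male household heads and community plays (Intervention description {11a}) can affect women who report no exposure, which undermines the exclusion restriction.

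The cost is a change of wording and a little analysis work, with no new data collection. The restricted analysis will have fewer women and a wider interval; by how much cannot be worked out, because the article does not say how many women live near an opposite-arm cluster.

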### Plans to give access to the full protocol, participant-level data and statistical code {31c}

Data will be made available on LSHTM’s Data Compass [34], along with project documentation and a data-users guide 12 months after the end of the study.

### Composition of the data monitoring committee, its role and reporting structure {21a}

Project monitoring will be led by Sightsavers, who will compile data from implementing partners to monitor intervention delivery.

### Adverse event reporting and harms {22}

Delivery of interventions will be monitored by Sightsavers; however, no severe adverse events are anticipated. The IFPLAN project only seeks to provide awareness of family planning options, how these can be accessed, and improving the accessibility of family planning services in Kaduna city. Interventions have been developed in close partnership with people with disabilities and the project aims for women to meet their own family planning needs, focusing on bodily autonomy and the rights of people with disabilities.

Sightsavers has a mechanism which is open to the public to report improper conduct through the Speak Up platform [35]. If anyone witnesses or suspects any safeguarding issues or misconduct within the project, they can report it anonymously using this platform—and an investigation will follow.

### Frequency and plans for auditing trial conduct {23}

Field supervisors will be responsible for quality assuring that work by the data collection teams is conducted per protocol and the data manager will conduct daily checks for the completeness, accuracy, and timeliness of data, following up with the data collection teams as required. During data collection, daily debrief sessions will be conducted to review work conducted.

### Plans for communicating important protocol amendments to relevant parties (e.g. trial participants, ethical committees) {25}

Modifications to the protocol that affect the conduct of the trial will be agreed upon by LSHTM and OPM Nigeria, and approved by the LSHTM Ethics Committee and the National Health Research Ethics Committee of Nigeria prior to implementation. Important protocol modifications will be updated on the trial registry.

### Dissemination plans {31a}

Findings from the trial will be shared with key stakeholders in Nigeria and published in peer-reviewed journals.

## Discussion

There is currently a dearth of information regarding effective interventions for inclusive access to sexual and reproductive health services for women with disabilities in LMICs [7]. However, defining access to services is complex, as it is not a single variable that can be measured directly [18]. Use of services is not equivalent to access, since (1) not everyone has an objective ‘need’ for services and (2) not everyone who has a need has a desire—or subjective ‘need’—to use services. For family planning, we might define objective need, (1), as fecund women who report that they would like to delay or permanently end having children while also having sexual relations with a fertile man. This raises a secondary issue, which is that this ‘objective’ need is based on the *subjective* desires that the woman has regarding family planning. Unlike for a condition that can be objectively assessed—such as HIV status—the need for family planning has only subjective components, both in determining that there is an issue that could be remedied with use of services, (1), and the desire to use services to address this need (2). Use is therefore realized access [18]. Unlike HIV, there is no comparable ‘treatment cascade’ either, since for any position on a cascade there is a reasonable choice, for example between having more children or not. In the context of persons with disability, this is particularly important when considering the position of women with disability who might be pressured into considering contraceptive methods against their will [36]. A further complication is that a woman’s desires for family-planning services can change over time, and so it is not possible to use her position at baseline as a guide to what ‘should’ be her position at endline.

Access is made up of several supply- and demand-side factors [18], with additional factors that affect only persons with disability [3, 4]. A complete assessment of access could ascertain whether someone who had a need and desire for service would be able to use them. However, this would only be successful if our model was correct, which for persons with disability, and many possible impairments, is unlikely. If the model is not correct then, for example, we might say that someone ‘has access’ to services when, in fact, there remained impediments (or lack of support factors) that would render the services inaccessible. If some of the impediments have been removed, then we could say her access has ‘improved’, while being aware that access has not been realized.

We have conceptualized ‘access to family planning’ for the purposes of this trial as shown in Table 2, to try to address these issues. This conceptualization takes account of the following characteristics of access in the context of this family-planning intervention:All women should know about available services if they are to have ‘access’;Women who want to delay or reduce future pregnancies should be able to realize ‘access’ through use of services;Women who do not want to delay or reduce future pregnancies, or are not in sexually active relationships, are not expected to have realized their ‘access’ to services through service use; instead, understanding access is a composite of their beliefs about using services if they needed them (hypothetically) and their impressions of the barriers or facilitators that we expect should determine use.

There remains a challenge with this conceptualization. Part of the effects of the intervention could be to increase voluntary demand for family planning, leading to an increase in the number of women who would like to delay or reduce future pregnancies. This might occur without a compensatory increase in the availability of services since the intervention has only limited influence over the provision of services. Demand will be included as a secondary outcome in anticipation of this eventuality.

Despite the challenges in measuring access, it is hoped that the evidence generated by this trial strengthens the evidence base on how to improve inclusive family planning for women with disabilities in Nigeria and other LMIC settings.

## Trial status

This manuscript is based on protocol version 3, 01 November 2022. Baseline recruitment and data collection started in December 2022. Endline and process evaluation recruitment and data collection is anticipated for 2024.

## Data Availability

Data will be made available on LSHTM’s Data Compass 12 months after the end of the study, along with project documentation and a data-users guide [34]. The data will be made available open access, ensuring that no identifiers are included in the data. Explicit consent has been included for making data open access.
